### Recruitment {15}

Eligible patients, who will be referred to the pedorthist for orthopedic shoes, will be informed about the study by the podiatrist and will receive the information brochure and informed consent form. The podiatrist will ask permission to send contact details to the research team. On receipt of that permission, the podiatrist will provide details of the patient to the coordinating investigator. The coordinating investigator will contact the patient in order to further explain the study and answer any questions the patient may have. During a multidisciplinary consultation with a pedorthist and a medical specialist, the patient will be asked if he/she decided to participate in this study. If he/she decided to participate, the investigator or the investigator’s representative will ask the patient to sign informed consent.

### Assignment of interventions: allocation

#### Sequence generation {16a}

Randomization will be performed at the level of the podiatrists. Based on their working location (distance from Voetmax Orthopedie locations), working calendar, working days, and number of patients with diabetes, we included 20 podiatrists of Voetencentrum Wender in this study. Since the podiatrists still differ widely in their number of patients seen and experience with the specific target group, stratified randomization will be used for the group of podiatrists. Four of the 20 podiatrists run special consultations for people with diabetes and are therefore likely more specialized in diabetic foot disease. These four podiatrists are split into two groups, based on the number of patients seen per year (based on the figures of 2019), and equally randomized to the group who receive MI training or to the group who do not receive MI training. The other 16 podiatrists are randomized next, also stratified by the number of patients seen per year (based on four strata using last year’s figures). The randomization is done centrally by an independent researcher using www.sealedenvelope.com.

Each podiatrist will exclusively provide either the MI intervention or usual care. Thereafter, the pedorthist will provide the new digital shoe-fitting procedure for the intervention group of participants or the casting-based shoe-fitting procedure for the control group.

#### Concealment mechanism {16b}

The participants have not randomized themselves, because the background assignment of the treating podiatrist (being trained in MI or not) will determine the treatment allocation of the participants. Randomization is performed at the level of the podiatrists to avoid contamination between intervention and control participants. Therefore, the randomization sequence will not be concealed from the podiatrists. Because each podiatrist will exclusively provide either the MI intervention or usual care, and thereafter, the pedorthist will provide the new digital shoe-fitting procedure for the intervention group of participants or the casting-based shoe-fitting procedure for the control group, and the randomization sequence will also not be concealed from the pedorthists.

All participant data is pseudonymized, but because the investigators have access to the coding of the personal data of the participants, the randomization sequence will also not be concealed from them.

#### Implementation {16c}

Not applicable, because participants will not be randomized. Randomization will be performed at the level of the podiatrists (see the “Sequence generation {16a}” section).

### Assignment of interventions: blinding

#### Who will be blinded {17a}

Blinding and concealed treatment allocation for podiatrists is not feasible, because of the way of randomization (see the “Concealment mechanism {16b}” section). Outcome assessments and analyses are not performed by independent staff, but by the investigators themselves, and therefore, they are also not blinded to the treatment allocation (see the “Concealment mechanism {16b}” section).

#### Procedure for unblinding if needed {17b}

Not applicable, because this is an open-label trial and because the outcome assessments and analyses are not performed by independent staff (see the “Concealment mechanism {16b}” section).

### Data collection and management

#### Plans for assessment and collection of outcomes {18a}

All standardized instruments used in the study procedure are described in Table 2. Information on the other study instruments can be found below.

##### Orthotimer® and reader device

The Orthotimer® microsensor (Rollerwerk Medical Engineering & Consulting, Balingen, Germany) will be used for continuous, long-term measurement of adherence and is a valid sensor to measure temperature in footwear [45]. The microsensor measures the temperature within the footwear every 15 min (96 measurements per day) and stores these data for 100 days before overwriting the oldest data. Longer observation periods will be possible by reading out the temperature microsensor data before this deadline. Every temperature microsensor reading will be stored with a date- and timestamp. In case participants will be prescribed more than one pair of orthopedic shoes, in both pairs of shoes, a temperature microsensor will be placed and data from both temperature microsensors will be combined.

The temperature microsensor is controlled with the wireless reading device and the saved wearing time dates are transferred to the respective software. The reading device can be connected with the computer via a USB plug. The software is used to control the temperature microsensor as well as to perform the wearing time analysis of the participant data.

##### Activity monitor

The Misfit Shine 2™ (Misfit Wearable, Burlingame, CA, USA) is a small tri-axial accelerometer which will be carried at the lower extremity. The Misfit Shine 2™ measures steps, calories burned, distance, activity types, sleep quality, and duration. The Shine 2 holds up to 30 days of activity data. The reliability of the Misfit shine is good [46]. Data can be transferred reliably and wireless to the Health app (iPhone) or Google Fit (Android phone), which will be connected to the TIIM-app (BMS Lab, University of Twente), so the data will be collected at a secured server.

##### Interview structure

The interviews will contain open-ended and closed questions and will be structured according to the relevant concepts for adherence to orthopedic shoes. To gain insight into the perspective of participants, motivations for and experienced advantages and difficulties regarding frequency, proper fit, and adequate wearing of orthopedic shoes will be discussed with the participants.

To examine the experiences of MI-trained podiatrists, the following topics will be discussed in the interview: knowledge, adoption and implementation of the motivational interviewing procedure among podiatrist, and their experiences and attitudes toward applying MI in this group of participants.

#### Plans to promote participant retention and complete follow-up {18b}

The patients will receive extensive information about the study setup and requirements during the recruitment. Once in the study, to promote complete follow-up, all participants receive a phone call before all their consultations during the study to remind them about the consultation (see the “Strategies to improve adherence to interventions {11c}” section).

#### Data management {19}

As required by the funder (ZonMw), a data management plan has been developed for this study. The participants will be coded by the letter of the participating center (one letter) and the letter of intervention or control group (one letter) followed by the number of the participant (four digits). All personally identifiable information will be saved in a locked cupboard with the coordinating investigator and on a computer protected with a password. All data will be collected on paper and then entered electronically in an Excel database by the investigator. All pseudonymized study data will be entered in a specific server facility (LISA) of the University of Twente for storage and archiving. The handling of the data will comply with the EU General Data Protection Regulation and the Dutch Act on Implementation of the General Data Protection Regulation (Uitvoeringswet AVG, UAVG). All study information will be saved for 10 years after the study ends in DANS (Data Archiving and Network Services). Access to original data on paper will be kept in a locked cupboard at the university with the coordinating investigator during the study.

#### Confidentiality {27}

All collected data will be pseudonymized by the coordinating investigator. The key code will be stored on a different secured server than the data and will be password protected. The principal investigator will decide who of the research group will have access to the data. Names of the participants will only be recorded on the informed consent form, which will be kept in a locked cupboard with the coordinating investigator, separated from the digital data and without a possibility to trace the data.

#### Plans for collection, laboratory evaluation, and storage of biological specimens for genetic or molecular analysis in this trial/future use {33}

Not applicable, because no samples will be collected.

## Statistical methods

### Statistical methods for primary and secondary outcomes {20a}

Statistical analysis and the cost-effectiveness analysis will be carried out with R environment for statistical computing (R Foundation, Vienna, Austria [47]). For statistical analyses, a significance level of *P* < 0.05 will be adopted.

#### Descriptive statistics

Anthropometric data, other participant characteristics, and data from adherence to orthopedic shoes and step count will be presented as mean or median with their standard deviation or the frequencies will be presented. Differences in the baseline characteristics between the participants receiving the novel care approach and usual care will be tested with a *t*-test, Mann-Whitney *U* test, chi-square test, or Fisher’s exact test, depending on the type of variables and being normally distributed or not.

#### Primary study outcome

Between-group differences in the proportion of participants who adhere to the use of their orthopedic shoes, that is, take at least 80% of their total steps with orthopedic shoes will be tested using a generalized linear mixed model (GLMM). A logistic link function will be used for the binary outcome on participant level (adherent yes/no) and random effects for podiatrists will be included.

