#### Methods in analysis to handle protocol non-adherence and any statistical methods to handle missing data {20c}

Between-group differences in the proportion of participants who adhere to the use of their orthopedic shoes, that is, who take at least 80% of their total daily steps with orthopedic shoes, will be tested in an intention-to-treat analysis using a generalized linear mixed model (GLMM) which can inherently deal with data missing at random.

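### The primary model, as described, has no term for the factors used to stratify podiatrists; the cost in precision is modest and adding two terms is cheap

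*Protocol article*

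**What the plan says.** Under Sequence generation {16a}, "Randomization will be performed at the level of the podiatrists". The protocol article explains that podiatrists vary in caseload and in experience with this patient group, and that for this reason "stratified randomization will be used for the group of podiatrists". Two factors are used:

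- **Specialist status.** "Four of the 20 podiatrists run special consultations for people with diabetes", and "These four podiatrists are split into two groups, based on the number of patients seen per year".
- **Volume among the others.** "The other 16 podiatrists are randomized next, also stratified by the number of patients seen per year", in four strata.

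That makes 2 + 4 = 6 strata for 20 podiatrists.

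Under Primary study outcome, the between-arm comparison is a generalised linear mixed model (GLMM) with a logistic link for the binary adherence outcome, and "random effects for podiatrists will be included". The section on non-adherence and missing data {20c} restates that the primary comparison "will be tested in an intention-to-treat analysis using a generalized linear mixed model (GLMM) which can inherently deal with data missing at random". Secondary study outcome extends the GLMM approach to the other endpoints. None of these sections names a stratum, specialist or caseload term, and none excludes one.

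The Discussion adds 12 MI-trained and 16 control podiatrists outside the stratified randomisation. It says that the 12 were those with the largest diabetes caseloads.

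**The concern.** When clusters are randomised within strata, differences between strata are balanced between arms by design and should not count as error in the arm comparison. A model with only a podiatrist random intercept does count them. They enter the estimated podiatrist variance and so the standard error of the arm effect. If specialist status or caseload is related to adherence, the test is then conservative and some power is lost.

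Second, stratification balances podiatrists, not the participants they go on to recruit. Recruitment follows an allocation that is not concealed from podiatrists (Concealment mechanism {16b}), and the Discussion reports slower inclusion in the intervention arm. If specialists or high-volume podiatrists recruit more in one arm than in the other, nothing in the described model adjusts for it.

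Precision is scarce here: the Discussion says that 220 participants is no longer realistic under the initial criteria, design and period.

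**Working it through.** **Inputs.** From Sample size {14}: 40% v 60% adherent, two-sided alpha 0.05, power 0.80, ICC 0.01, 200 evaluable participants. From Sequence generation: 20 podiatrists. Assumptions: 10 podiatrists per arm and equal recruitment, so m = 10 participants per podiatrist and 100 per arm.

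**Step 1: reproduce the plan's figure.** The variance sum is 0.4 × 0.6 + 0.6 × 0.4 = 0.48. Without clustering, n per arm = 0.48 × (1.960 + 0.842)² / 0.2² = 94.2. Solving for cluster size with design effect 1 + (m − 1) × 0.01 and 10 podiatrists per arm gives m = 10.29, or 205.9 in total. This is within 3% of the stated 200, and power at 200 is 0.790. The plan's figure is reproduced.

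**Step 2: what stratum terms can gain.** They can remove only between-podiatrist variance. If they explain a share s of it:

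DE = 1 + 9 × ICC × (1 − s); SE = √(0.48 × DE / 100); power = Φ(0.2 / SE − 1.96)

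| ICC | s | DE | SE | Power |
|---|---|---|---|---|
| 0.01 (plan) | 0 | 1.090 | 0.0723 | 0.790 |
| 0.01 | 0.5 | 1.045 | 0.0708 | 0.806 |
| 0.01 | 1 | 1.000 | 0.0693 | 0.823 |
| 0.05 (assumed) | 0 | 1.450 | 0.0834 | 0.669 |
| 0.05 | 0.5 | 1.225 | 0.0767 | 0.742 |
| 0.05 | 1 | 1.000 | 0.0693 | 0.823 |

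At the plan's ICC the largest possible reduction is 0.09 / 1.09 = 8.3% of the variance, or 4.2% of the standard error.

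**Step 3: charge for degrees of freedom.** With a t reference, the unadjusted model has 20 − 2 = 18 podiatrist-level degrees of freedom, and two added terms leave 16.

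- ICC 0.01: power is 0.744 unadjusted. With two terms it is 0.738 if they explain nothing and 0.773 if they explain everything: a loss of 0.6 points at worst, a gain of 2.9 at best.
- ICC 0.05: power is 0.621 unadjusted. With two terms it is 0.688 (half explained) or 0.773 (all explained).
- Five stratum dummies leave 13 degrees of freedom. At ICC 0.01 the best case is then only 0.761.

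**Step 4: simulation.** The model was a logistic GLMM with a Wald z test, fitted without and with five stratum dummies (20 podiatrists × 10 participants, six strata, 1,500 runs per scenario). The Monte Carlo error of a 5% rejection rate is √(0.05 × 0.95 / 1500) ≈ 0.006.

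| ICC | Share explained | Power without / with | Type I error without / with |
|---|---|---|---|
| 0.01 | 1 | 0.793 / 0.821 | 0.041 / 0.049 |
| 0.01 | 0.5 | 0.785 / 0.822 | 0.043 / 0.057 |
| 0.05 | 1 | 0.663 / 0.784 | 0.027 / 0.053 |
| 0.05 | 0.5 | 0.665 / 0.757 | 0.044 / 0.073 |
| 0.10 | 1 | 0.479 / 0.777 | 0.008 / 0.055 |
| 0.10 | 0.5 | 0.544 / 0.698 | 0.032 / 0.080 |

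The empirical spread of the estimate was about the same in both models. At ICC 0.05 with everything explained, under the planned effect, it was 0.303 without and 0.314 with the dummies, while the median model-based SE fell from 0.343 to 0.303. The loss therefore lies in the reported standard error. At ICC 0.01 this excess is barely visible: under no effect, SE 0.286 against an empirical spread of 0.287 without strata. The type I rates of 0.073 and 0.080 show that a plain Wald test with many podiatrist-level terms can be anti-conservative. The two-term model was not simulated.

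**Step 5: all 48 podiatrists.** Assuming the first 20 split evenly, the arms hold 10 + 12 = 22 and 10 + 16 = 26. With 200 participants, m = 200 / 48 = 4.17 and DE = 1 + 3.17 × 0.01 = 1.032. Power is 0.808, rising to at most 0.820.

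**The case against.** The strongest objection is that the point rests on silence. A condensed article names the model family, the link and the random effect; a covariate list often sits in the full protocol or the SAP, neither of which is shown. A reader might infer that the strata were deliberately excluded. The text does not support that, since it neither includes nor rules them out. What remains is that the article fixes the model down to its random effect in two places, and that terms for the randomisation factors would improve the model so described.

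A reader might also infer that the precision gained by stratifying is lost altogether. That does not hold either. The balance from stratified assignment is kept, the unadjusted test is at most slightly conservative at the plan's ICC, and the gain available there is 1.6 points if the strata explain half and 3.3 points if they explain all. Larger gains need an ICC that the document does not give.

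Three further objections stand in part:

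- The article says that podiatrists differ in volume and experience, not that these predict adherence. The share explained is unknown.
- Two main effects do not reproduce six nested strata, so the all-explained figure is an upper limit and not a forecast for the proposed terms.
- Only 20 of 48 podiatrists were assigned by stratified randomisation. This shrinks the power argument, but it gives the same terms another use: the added MI-trained podiatrists were picked for high diabetes caseload, so caseload may now differ between arms by selection.

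**Conclusion.** The point holds as a modest one. The described primary model does not reflect the stratified allocation of the original 20 podiatrists. Its standard error therefore tends to be somewhat too large, and differences in recruitment by stratum go unadjusted.

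At the plan's ICC of 0.01 the cost is at most about 3 power points with 20 podiatrists and about 1 with 48. At an assumed ICC of 0.05 with 20 podiatrists it would be about 7 points (half explained) to 15 points (all explained). These figures rest on equal cluster sizes, an even split of podiatrists, a normal approximation and an unknown share explained. The error is in the conservative direction, so the analysis is not invalid.

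Adjustment would also account for measured caseload differences between arms. It would not restore randomisation for the 28 added podiatrists, and it should not be presented as doing so.

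**What to change.** Before the analysis, state that the primary GLMM and the secondary GLMMs comparing participants between arms include two podiatrist-level fixed effects, diabetes-specialist consultation (yes/no) and log patients seen per year, alongside the podiatrist random effect. Test the arm effect against a small-sample t-type reference and not a plain Wald z. Two terms are preferable to five stratum dummies, which use more degrees of freedom. Use the caseload figure from the randomisation for the original 20 podiatrists, and a comparable figure from before recruitment for the 28 added later.

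Cost: a sentence or two of analysis-plan wording, two podiatrist-level degrees of freedom (about 0.6 power points at ICC 0.01 with 20 podiatrists if the terms explain nothing), and retrieval of specialist status and caseload for the added podiatrists, whose figures the article does not show to be held. The odds ratio also becomes conditional on the two covariates, and the report should say so.

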#### Secondary study outcome

Differences in the level of adherence to the use of orthopedic shoes of participants and differences in the proportion of participants (re-)experiencing complications after receiving their orthopedic shoes, up to 1 year after baseline between the two groups of participants will also be tested using appropriate generalized linear mixed models. The quantitatively measured aspects of the participant experiences and the experiences of the MI-trained podiatrist will be tested using the same approach. The type of GLMM depends on the variable that will be tested in the model.

The qualitative (verbal) interview data of the experiences of the participant and the MI-trained podiatrist will be summarized with two code schemes (one for the participants’ experiences and one for the podiatrists’ experiences). The code schemes will be developed by combining inductive and deductive thematic analysis. Content and frequency of the main themes will be compared for the two groups of participants, and this information will be triangulated with the quantitative information on the experiences of participants to explain in more depth the results of adherence and in order to formulate implementation recommendations from the patients’ perspective. This triangulation approach will also be applied for the quantitative and qualitative data of the MI-trained podiatrists.

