### Eligibility criteria {10}

In order to be eligible to participate in this study, a participant must meet all of the following inclusion criteria:
A clinical diagnosis of diabetes mellitus type 1 or 2Aged 18 years or olderWith or without previous callusWith or without previous ulcersIdentified with risk profiles 2, 3, or 4, according to the “zorgmodule preventie diabetische voetulcera 2014” [30]. Internationally better known as the IWGDF Risk 1–3 [31], see Table 1

**Table 1 Tab1:** Care profiles 2–4 versus IWGDF Risks 1–3 for eligible patients

Care profile	Category	Ulcer risk	Characteristics
2	1	Moderate	LOPS + PAD
3	2	Moderate	LOPS + foot deformity
			PAD + foot deformity
4	3	High	LOPS or PAD, and one or more of the following: - History of a foot ulcer - A lower-extremity amputation - End-stage renal disease

*LOPS* loss of protective sensation, *PAD* peripheral artery diseaseEligible for a prescription of orthopedic shoes

Participants will be excluded when they meet any of the following exclusion criteria:
Did not receive orthopedic shoes, but instead an adaption to confection shoes or semi-orthopedic shoesHave a foot ulcerActive Charcot’s neuro-arthropathyHave a foot infectionUnable to walkUnable to read and understand the study instructions

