#### Complications

The proportion of participants (re-)experiencing complications (i.e., one or more ulcers or abundant callus that requires debridement, not present at baseline, or lower-extremity amputation) will be determined by the registration of (re-)experienced complications after receiving their orthopedic shoes, up to 1 year after baseline. All complications will be registered and photographed by podiatrists, who are informed by the participant if complications occur (in > 95% of complications cases, the podiatrist is the first to hear from the participants). If it is necessary to obtain details on specific complications, general practitioners or orthopedic surgeons will be contacted. Photographs will be assessed by observers blinded to treatment allocation to confirm the type and/or severity of the complication.

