#### Time point “− T1”—inclusion

After referral of the podiatrist, the pedorthist and medical specialist will decide together, during a multidisciplinary consultation, which type of shoes the patient will need. When instead of custom-made orthopedic shoes convection shoes or semi-orthopedic shoes will be prescribed, the patient cannot be included in the study. After the patient has been prescribed custom-made orthopedic shoes, he/she will be asked if he/she decided to participate in this study, and the investigator or the investigator’s representative will ask the patient to sign informed consent. Also, the demographic data (age, gender, ethnicity, height, and weight), diabetes type and duration, risk profile, ambulatory status, history regarding the use of orthopedic shoes, educational status, socioeconomic status, and capacity for self-care are completed. Subsequently, data on the presence of peripheral artery disease, peripheral neuropathy, foot deformities, and history of previous foot ulceration and amputation will be recorded, and the participants will be asked to fill in specific questionnaires (time point “− T1” at Table 2).

Thereafter, during a consult with the pedorthist, the orthopedic shoes will be fitted. The pedorthist will provide the new digital shoe-fitting procedure or the casting-based procedure depending on whether the podiatrist is trained in MI or not.

Within 1 to 6 weeks, the participant from the intervention group will have another consultation with the MI-trained podiatrist (first consult: participant was referred to the pedorthist). The podiatrist will apply MI in this conversation. From all included participants, thirty participants, 15 from both groups, will be approached for an in-depth interview about their perspective on and experiences with orthopedic shoes before receiving these shoes. This interview will be performed by one of the investigators.

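### No adjustment for baseline foot-risk category is stated for the complications comparison, although podiatrists were added outside the described randomization and case mix may differ between arms

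*Protocol article*

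**What the plan says.** The section Secondary study outcome compares "differences in the proportion of participants (re-)experiencing complications after receiving their orthopedic shoes, up to 1 year after baseline"; the comparison "between the two groups of participants will also be tested using appropriate generalized linear mixed models". It adds that "The type of GLMM depends on the variable that will be tested in the model". No covariate is named and none is ruled out. For the primary outcome, the article names a logistic link and says that "random effects for podiatrists will be included". The section Descriptive statistics has baseline characteristics tested between arms, with no consequence attached to the result.

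A complication is "one or more ulcers or abundant callus that requires debridement, not present at baseline, or lower-extremity amputation", counted per participant. Table 1 under Eligibility criteria {10} rates the two lower risk categories as moderate and the third as high. The third requires loss of protective sensation or peripheral artery disease plus one further feature: "History of a foot ulcer", an amputation or end-stage renal disease. At time point −T1 the risk profile is recorded, and "data on the presence of peripheral artery disease, peripheral neuropathy, foot deformities, and history of previous foot ulceration and amputation will be recorded".

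Sequence generation {16a} describes 20 podiatrists randomized with stratification. Four of them "run special consultations for people with diabetes and are therefore likely more specialized in diabetic foot disease" and are split equally between arms. The Discussion then reports 12 further MI-trained podiatrists, selected because they see most patients with diabetes. It says that this departs from the stratified randomization of the first group. It also reports 16 further control podiatrists and describes no randomization for them. Under Concealment mechanism {16b}, allocation is known to podiatrists and pedorthists. Under Recruitment {15} and the screening time point, the podiatrist first informs the patient and passes on contact details.

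**The concern.** Ulcer prevention is part of the stated aim, and the complications comparison is its clinical test. The baseline feature by which the article itself grades ulcer risk does not appear in the described analysis.

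If podiatrists had entered the arms only by randomization, a difference in case mix would be chance, and the clustered standard error would allow for it. Once podiatrists enter an arm by selection, and recruiters know the arm, the expected case mix can differ. A random effect for podiatrist describes variation around each arm's mean. It does not correct a difference between those means, so a difference in patient risk could be read as an effect, or a lack of effect, on ulcer prevention.

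**Working it through.** **1. What is stated on adjustment.** Primary outcome: random podiatrist effect, no fixed covariate named. Complications: an appropriate mixed model, with its type left to depend on the variable. Baseline differences: significance tests, no action. The Discussion lists the most important design changes, and none of them touches the analysis.

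**2. How much of the allocation lies outside the described randomization.** Taking the added podiatrists as additional to the first 20: 20 + 12 + 16 = 48 podiatrists, of whom 12 + 16 = 28, so 28/48 = 58%. This counts podiatrists. The article does not say how many participants each contributes.

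**3. The plan's own figure.** None is given for complications. The stated total of 200 concerns adherence (40% v 60%, two-sided alpha 0.05, power 0.80, intraclass correlation 0.01). Assuming 10 participants for each of 20 podiatrists, the design effect is 1 + (10 − 1) × 0.01 = 1.09. Power at 200 is Φ(0.20/√(0.48 × 1.09/100) − 1.96) = Φ(2.765 − 1.96) = 0.79. The figure reproduces closely but does not bear on this point.

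**4. Spurious difference with no treatment effect (assumed inputs).** Spurious difference = (difference in high-risk share) × (difference in risk between categories).
- Risks 15% and 35%: 0.10 × 0.20 = 0.02; 0.20 × 0.20 = 0.04.
- Risks 10% and 40%: 0.10 × 0.30 = 0.03; 0.20 × 0.30 = 0.06.

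The range is 2 to 6 percentage points.

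**5. Odds ratio by hand (assumed inputs).** Risks 10% and 30%; high-risk share 40% (novel care) v 60% (usual care).
- Novel care: 0.4 × 0.30 + 0.6 × 0.10 = 0.18.
- Usual care: 0.6 × 0.30 + 0.4 × 0.10 = 0.22.
- Odds ratio: (0.18/0.82)/(0.22/0.78) = 0.78.

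With the shares reversed it is 1.28.

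**6. Simulation (assumed inputs, true effect nil).** Ten podiatrists per arm with 10 participants each; log-odds of high risk varying between podiatrists with SD 0.5; complications depending only on risk category; 1,500 replicates. The model was logistic with cluster-robust standard errors, as a stand-in for the mixed model.

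| High-risk share, novel v usual | Risk, lower v high category | Unadjusted OR | False-positive rate | Adjusted OR | False-positive rate |
|---|---|---|---|---|---|
| 50% v 50% | 10% v 30% | 1.00 | 4.7% | 0.99 | 6.0% |
| 50% v 50% | 5% v 40% | 1.00 | 5.6% | 1.01 | 5.4% |
| 45% v 55% | 10% v 30% | 0.89 | 5.5% | 1.01 | 4.6% |
| 45% v 55% | 5% v 40% | 0.83 | 9.1% | 1.00 | 5.7% |
| 40% v 60% | 10% v 30% | 0.79 | 9.1% | 1.02 | 4.3% |
| 40% v 60% | 5% v 40% | 0.68 | 17.6% | 0.99 | 5.3% |

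The first two rows show that, with equal expected case mix, the unadjusted clustered test keeps about its 5% level. The others show what a systematic difference does. Adjustment removes it completely here because the simulated imbalance lies wholly in the measured category.

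**7. Which covariate.** By Table 1 every eligible participant has loss of protective sensation or peripheral artery disease. Either of these with a previous ulcer gives category 3, so previous ulcer is nested within category 3. A second term would only separate category 3 participants with an ulcer history from those who qualify by amputation or end-stage renal disease alone.

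**The case against.** The strongest reply is that the article is silent on covariates and does not rule them out. The model for a secondary outcome is described only in outline, and a covariate list is commonly left to an analysis plan or full protocol that is not shown. That stands against saying that the comparison is unadjusted, or that its model must match the primary one. A reader might infer either; the text supports only that no adjustment is stated.

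A reader might also infer from the four specialised podiatrists that high-risk participants will cluster in one arm. The document does not support this: those four are divided equally by stratified randomization, and the other 16 of the original group are stratified by volume. For those 20, chance imbalance is carried by the standard error, and adjustment would mainly serve precision.

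It is also fair that the complication risks and imbalances above have no source in the document, that patient volume is not risk category, and that the outcome includes callus needing debridement, so the gradient across categories may be weaker than assumed. Pooling first and recurrent events is no error, since the outcome is defined per participant and both groups are deliberately eligible.

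What the reply does not meet is the change described in the Discussion. The article discloses allocation by selection, together with recruitment under known allocation, and its only stated response to baseline differences is testing them.

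**Conclusion.** The point holds in a limited form and is worth acting on. As written, the analysis states no adjustment for foot-risk category. The later addition of podiatrists and the open allocation create a route to systematic case-mix differences that a podiatrist random effect does not remove. Direction and size cannot be derived. The 2 to 6 points and the odds ratios of 0.68 to 0.89 are illustrations on assumed risks, and reversing the imbalance would bias against the novel care approach instead. A reader might conclude that the ulcer-prevention result will be spurious; the document shows only that it is exposed. The outcome is secondary, so this does not undermine the primary comparison by this argument.

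**What to change.** State in advance that the complications mixed model includes, besides arm and the podiatrist random effect, a fixed effect for baseline risk category (IWGDF 1–2 v 3, recorded at −T1), and that the unadjusted result is reported beside it. The adjustment should not depend on the baseline significance tests. Previous ulcer may replace risk category or be added as a refinement, but need not be a second required term.

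This should be fixed before analysis, because the section Who will be blinded {17a} has unblinded investigators performing the analyses, and a covariate chosen afterwards would carry less weight.

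The cost is wording only, since the data are collected. The downsides are an odds ratio that is also conditional on risk category, one extra parameter, and limited precision if events are few. Adjustment addresses the measured category and does not restore randomization, so other differences between the added podiatrists' patients could remain.
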